**Fig. 1 Fig1:**
[figure not shown]
KEMRI and CDC Health and Demographic Surveillance System. **a** Location of western Kenya in Kenya. **b** Location of KEMRI and CDC Health and Demographic Surveillance System (HDSS) in western Kenya. **c** Mass test and treat clusters within KEMRI and CDC HDSS

Malaria transmission is high and occurs year-round with two peak transmission seasons in May–July and November–December, coinciding with the end of the long and short rains, respectively. LLIN distribution campaigns and the roll-out of ACT and RDTs have been supported in this area through the KEMRI and CDC collaboration and with other partners including the Kenya National Malaria Control Programme, the U.S. President’s Malaria Initiative, and the Global Fund to Fight AIDS, Tuberculosis, and Malaria. Since the widespread introduction of insecticide-treated nets into the HDSS area in 1997, malaria prevalence by microscopy has decreased in children aged 1–5 years from >70% [35] to approximately 39% in 2013; *P. falciparum* is the predominant malaria parasite species comprising >95% of all infections [36]. The proportion of community members with infections detected by microscopy who did not report a fever in the previous 2 weeks varies by age and is >90% in many age groups [[name], personal communication].

Since mortality data have been collected in the HDSS using verbal autopsy methods, there has been a threefold reduction in the malaria-specific mortality rate in children <5 years from 13.2 per 1000 person-years in 2003 to 3.7 per 1000 person-years in 2010 [37]. The number of malaria infective mosquito bites per night dropped from approximately 300 in the early 1990s [38] to <20 in 2010, and the vector population temporarily shifted from *Anopheles gambiae s.s.* and *Anopheles funestus* to *Anopheles arabiensis* before *An. funestus* re-emerged as the primary vector [39]. Household ownership of at least one LLIN, universal coverage (defined as 1 bed net per every two persons per household), and use prior to study initiation were 81, 67, and 57%, respectively [[name], personal communication]. Indoor residual spraying has not been implemented as a programmatic strategy in Siaya County.

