### Measurement of malaria transmission outcomes

Four separate strategies were used to evaluate outcomes related to malaria transmission: (1) annual population-based cross-sectional studies for malaria prevalence, (2) active surveillance for malaria infection utilizing a longitudinal cohort, (3) passive surveillance of laboratory-confirmed clinical malaria cases in study health facilities, and (4) entomological transmission indices. Eligible participants residing within a household located within the core area were included in the sampling frame for study evaluations and analyses. Inclusion criteria, sample sizes, and main malaria transmission outcomes for each of the evaluations can be found in Table 1.

**Table 1 Tab1:** Inclusion criteria, sample size, and main outcome by evaluation type

Evaluation type	Inclusion criteria	Sample size	Main outcome
Cross-sectional studies	≥1 month of age	857 per arm	Community malaria prevalence
Longitudinal cohort study	≥1 year of age, not pregnant at time of recruitment	330 per arm	Incidence of malaria infection
Passive surveillance	Living within the core area of a cluster	N/A	Incidence of clinical malaria
Entomological surveillance	Household in either a control or intervention cluster	120 control and 60 intervention households per month	Monthly *P. falciparum* oocyst and sporozoite rates, *Anopheles* parity rate

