#### Entomological transmission indices

Monitoring was conducted to assess the impact of MTaT on entomological indices of malaria transmission by comparing the proportion of *Anopheles* mosquitoes with *P. falciparum* sporozoite and oocyst infections, and the parity rate, by study arm.

Each month, a simple random sample of twelve and six houses were selected (without replacement) from each of the ten control and intervention clusters, respectively, for pyrethrum spray catches (PSCs). Briefly, white sheets were placed over the surface of the floor and furniture between 0600 and 1200 h, and two collectors (one inside and one outside the house) sprayed around the eaves with 0.025% pyrethrum emulsifiable concentrate with 0.1% piperonyl butoxide in kerosene. The collector inside the house then sprayed the roof and walls of the house, and the house was closed for 10–15 min. Dead mosquitoes were then collected and placed on moist filter paper inside of petri dishes and returned to the laboratory.

Live collections using Prokopack [46] aspirators were performed for one week each month in each study arm. During the live sampling week, collectors visited as many households as possible until 1200 h. To maximize the number of specimens collected, the live collection methodology did not use a random sample. In each house, collectors spent 15–20 min aspirating mosquitoes, and those collected from the same house were placed into a single cage.

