#### Laboratory testing of mosquitoes

Mosquitoes collected during PSCs and live collections were first identified to species using morphological keys [52], while sibling species were identified by rRT-PCR for all *Anopheles gambiae s.l*. [53] and a subset of *An. funestus s.l*. [54] for the rRT-PCR identification of *An. gambiae s.l*., only the universal, the *An. gambiae s.s*. and the *An. arabiensis*, primers were used as these two species are the only ones known from this area. A subset of freshly collected, unfed mosquitoes were dissected and examined for parity status [55]. Fed, gravid and half-gravid mosquitoes were held for 5–10 days and midguts were dissected, stained with mercurochrome and then examined at 100× for the presence of oocysts. *P. falciparum* sporozoite rates in *Anopheles* mosquitoes were determined by sandwich ELISA [56, 57].

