### Data analysis

The primary outcome of incidence and prevalence analyses, in the cohort and cross-sectional studies, respectively, were microscopically confirmed *P. falciparum* parasitaemia. Arm-specific unadjusted prevalence ratios (PR) for parasitaemia and anaemia were calculated using data from the series of pre- and post-intervention cross-sectional surveys. These data were analyzed with a log-binomial model using generalized estimating equations to account for clustering. Pre- and post-intervention PRs between arms were evaluated using the same model. The incidence of clinical malaria, diagnostically confirmed by either RDT or microscopy, presenting to the MTaT study health facilities (passive surveillance) was calculated. Total case counts originating from each study arm at each health facility per month was divided by the total population of the study arm residing in the catchment area of the health facility according to the HDSS. The incidence of infection was determined from the cohort data. A Cox-Proportional Hazards model was used to compare time to infection between arms. Adjusted models were created to account for confounders including socioeconomic status, anti-malarial use, and LLIN use. Socioeconomic status (SES) was assessed using principal component analysis models of household assets [58]. Sporozoite and oocyst rates were compared by logistic regression using generalized estimating equations to account for correlated observations within the households. All analyses were performed using SAS statistical software version 9.3 (SAS Institute, Carey, NC).

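### The sporozoite and oocyst comparison takes all Anopheles as one group with no vector covariate named, although species group is recorded for every mosquito: a modest precision loss for spray catches, a stronger case for oocysts

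*Protocol article*

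**What the plan says.** Sporozoite and oocyst rates in vectors are one of the article's specific primary objectives (Study objectives). The section on entomological transmission indices defines the comparison as "comparing the proportion of *Anopheles* mosquitoes with *P. falciparum* sporozoite and oocyst infections, and the parity rate, by study arm". The genus is thus one denominator. Table 1 gives the main outcome as "Monthly *P. falciparum* oocyst and sporozoite rates, *Anopheles* parity rate".

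The model is given in one sentence under Data analysis: "Sporozoite and oocyst rates were compared by logistic regression using generalized estimating equations to account for correlated observations within the households". It names no species, month or season term. The adjustment variables listed in the same paragraph (socioeconomic status, anti-malarial use, net use) describe people and households, not vectors.

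On species, the section on laboratory testing says that mosquitoes from both collection methods "were first identified to species using morphological keys". All *An. gambiae s.l.* are then typed to sibling species, but only a subset of *An. funestus s.l.* Study area and population reports that at this site "the vector population temporarily shifted from" *An. gambiae s.s.* and *An. funestus* to *An. arabiensis*, and that *An. funestus* later became the main vector again.

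There are two collection methods. For spray catches: "Each month, a simple random sample of twelve and six houses were selected (without replacement) from each of the ten control and intervention clusters, respectively". In the aspirator collections, run one week a month in each arm, "the live collection methodology did not use a random sample".

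**The concern.** Where vector species differ in infection rate and the mix differs from cluster to cluster, the infected proportion over all Anopheles moves with the mix as well as with transmission. The intervention tests and treats people, so it is not expected to alter which species are caught. Species group is then a legitimate covariate, and leaving it out keeps avoidable between-cluster variation in a primary comparison.

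The oocyst outcome raises a second issue. Oocysts are read in mosquitoes held for 5 to 10 days before dissection. Spray catches yield dead mosquitoes, so these specimens must come from the live collections. Collectors there visited as many houses as they could before noon, and the article fixes no allocation over clusters. A difference between arms in species or timing could arise from where and when collectors worked, and randomisation does not protect against that.

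**Working it through.** **1. The article's own figure.** 10 clusters × 12 houses = 120 and 10 × 6 = 60, which agrees with Table 1 ("120 control and 60 intervention households per month"). The article gives no power calculation, infection rate, mosquito count or between-cluster variation for the entomological outcomes, so nothing further can be reproduced. All inputs below are assumptions unless a section is named.

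**2. How far a difference in mix moves the ratio.** Take two vector groups with infection-rate ratio R, a high-rate share averaging 60%, no intervention effect, and arms that differ by 10 points (65% v 55%):

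ratio = (0.65R + 0.35) / (0.55R + 0.45)

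- R = 1: 1.00
- R = 2: 1.65/1.55 = 1.06
- R = 3: 2.30/2.10 = 1.10
- R = 5: 3.60/3.20 = 1.13

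**3. Bias or noise?** Simulating 10 v 10 clusters under randomisation, the ratio due to mix alone centres on 1.00 in every setting. At R = 3 its 95% chance range is:

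| SD of cluster share | Independent clusters | Within-facility correlation 0.7 |
|---|---|---|
| 10 points | 0.92–1.08 | 0.96–1.04 |
| 20 points | 0.85–1.17 | 0.92–1.09 |

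For spray catches this is random error.

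**4. Share of the variance that a species term removes (spray catches).** Further assumptions: 2 Anopheles per house, 24 months, and between-cluster CV of risk 0.25. One intervention and two control clusters per facility, the control pair merged, follows Study design. Mosquitoes: 60 × 24 × 2 = 2,880 intervention and 120 × 24 × 2 = 5,760 control. With high rate h, low rate l, mean share s and overall rate p = s·h + (1 − s)·l:

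- sampling: A = 1/(2,880p) + 1/(5,760p)
- cluster risk: B = 0.25² × (1/10 + 1/20) × (1 − ρ)
- species mix: C = [(h − l)/p]² × SD² × (1/10 + 1/20) × (1 − ρ)
- approximate cut = C/(A + B + C)

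Here ρ is the within-facility correlation, applied to both risk and share.

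Low end (3% v 1%, s = 50%, SD 10 points, ρ = 0): p = 2%, A = 1/57.6 + 1/115.2 = 0.0260, B = 0.0094, C = 1² × 0.01 × 0.15 = 0.0015. Cut = 0.0015/0.0369 = 4%.

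High end (3% v 0.3%, s = 50%, SD 20 points, ρ = 0): p = 1.65%, A = 1/47.5 + 1/95.0 = 0.0316, B = 0.0094, C = 1.636² × 0.04 × 0.15 = 0.0161. Cut = 0.0161/0.0571 = 28%.

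With ρ = 0.7, B and C are multiplied by 0.3:

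- low end: 0.00045/(0.0260 + 0.0028 + 0.00045) = 1.5%
- high end: 0.0048/(0.0316 + 0.0028 + 0.0048) = 12%

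Simulation of crude against species-stratified estimates agrees: about 4–28% with independent clusters and 2–13% with ρ = 0.7. With one group at 80% of the catch and ρ = 0.7, the formula gives 1–8%. Simulation, in which a share cannot exceed 100%, gives about 1% to 6 or 7%. No setting showed a loss.

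In standard-error terms, a 13% variance cut is 1 − √0.87 = 7%, and a 28% cut is 1 − √0.72 = 15%.

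**5. Calendar time.** For spray catches each cluster pair contributes 12 and 6 houses every month, a constant 2:1. Month is therefore roughly balanced by design, and only mosquito yield per house can differ. For live collections there is one week a month per arm, no fixed number of houses and no stated spread over clusters, so that balance cannot be assumed.

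**The case against.** The strongest reply is that the article nowhere says species are pooled in the model. It is a condensed report, and covariate lists commonly sit in a fuller plan that is not shown. That is fair as far as the model sentence goes, and silence on covariates would not alone support the point. But the outcome itself is defined over Anopheles as one group, and the paragraph that does name adjustment variables names none for vectors.

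Second, clusters were randomised within facility areas, partly to limit spatial differences in transmission. The reported change of vectors happened over time at the site, so it is no evidence that neighbouring clusters differ. This stands, and it is why the smaller range is the more plausible one.

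A reader might infer more than the documents support:

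- **That months are pooled.** This is not stated. Table 1 speaks of monthly rates, and spray catches are fixed by month.
- **That the species mix is bound to be unequal between arms.** It may be, but randomisation makes no arm more likely to carry the surplus.
- **That the spray-catch comparison is biased.** It is not. The mix adds noise.
- **That the gain is large.** Bigger cuts need ten independent clusters against ten, an even species split and wider spread. The article supports none of these, and the first sits badly with the matched design.

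Incomplete sibling typing of *An. funestus* is no obstacle, because *An. funestus s.l.* can serve as one group. A species term also does not settle whether household is the right correlation unit when clusters were randomised. That is a separate matter.

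**Conclusion.** The point holds as a worthwhile improvement to a primary comparison, not as an error that invalidates it. For spray catches, species adjustment would cut the variance of the log rate ratio by roughly 1–13% if species mix is correlated 0.7 within facility areas, and by up to about 28% if it is uncorrelated. It would cut nothing if species rates or mixes are alike. These figures rest on assumed species rates (3% v 1% to 3% v 0.3%), cluster-share SD (10–20 points), average share (50–80%), catch per house and between-cluster CV, none of which the article gives.

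The case is stronger for oocysts, because the non-random live collections could let species or timing differ between arms through the sampling. That part is reasoned from the described methods. Its size cannot be computed from the article.

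**What to change.** In the sporozoite and oocyst models, add species group as a fixed covariate with three levels: *An. gambiae s.s.*, *An. arabiensis* and *An. funestus s.l.* Add season or grouped month at least in the oocyst model. Report the adjusted odds ratio with the crude one beside it. If a fuller plan already contains these terms, the article need only say so.

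The cost is a sentence or two in the analysis section, and no new data. The small downside is a few more model terms when positives are sparse, which is why months should be grouped and not fitted singly. Adjustment can remove measured differences in species and timing from the oocyst comparison, but it does not turn the live collections into a random sample. The report should say so.

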## Discussion

Previous results of trials or programmes incorporating mass campaigns, such as MTaT, for transmission reduction on a large-scale have been contradictory or inconclusive [31, 32]. As the population of individuals harbouring asymptomatic infections has been increasingly implicated in sustaining malaria transmission there has been renewed interest in evaluating time-limited MTaT in different transmission settings with high coverage of malaria control interventions for rapid malaria transmission reduction. The study site in western Kenya provided distinct advantages for evaluating MTaT including; (1) high malaria transmission despite high coverage with LLINs, (2) the existence of a HDSS through which sampling frames and population level data including births, deaths, and migration have been continuously monitored, (3) over 30 years of historical data on epidemiological and entomological malaria indices, (4) advanced laboratories and research infrastructure, and (5) strong relations with the communities and public and private health sectors in the region. In this manuscript, the strengths and limitations of the study design choices are discussed.

Interventions such as MTaT are designed to be effective at high coverage levels and, therefore, must be evaluated at the community level, but the cost and complexity of cluster-randomized trials combined with the heterogeneity of malaria transmission and differential access to health care complicate the design of such trials. To minimize differences in the spatial distribution of malaria transmission, differences in treatment availability and provider proficiency, the effect of distance on health-care seeking, and LLIN coverage, each cluster around the study health facilities was randomly assigned to the intervention or control arm, and only villages with a centroid within 3 kms from the health facilities were included. The result of this decision was that clusters abutted one another and were relatively small for campaign-style interventions, which are intended to be implemented over larger geographic spans for transmission reduction. This smaller size and geographic proximity may artificially increase the impact of migration as individuals may be more likely to migrate out of a smaller geographic cluster than a larger one, and through daily movement, may be more likely to enter a cluster that is closer to where they reside than one that is geographically distant.

Migration is known to play a major role in malaria transmission as parasites are transported from one area to another [59], or one cluster to another. In this trial, migration and contamination of parasites into other clusters, was likely non-differential, and thus may bias the outcome to the null. It was recognized that human migration was unavoidable and would serve as a limitation to evaluation, and measures were taken to quantify it during MTaT rounds, at cohort visits, and through the HDSS census, however daily movement between clusters was not quantified. To mitigate the impact of daily movement on the outcome measure while maintaining statistical tenets for cluster numbers, there was a consideration for creating much larger clusters that were geographically distant from one another, while maintaining the same number of clusters for statistical validity. However, this would have been cost-prohibitive and the necessary geographic separation would likely have led to significant confounding from transmission differences and health facility associated factors such as stockouts and care-seeking behaviour. When choosing a study design, researchers must carefully weigh the benefits of bias mitigating decisions versus the introduction of contamination. Smaller clusters were used in this study. Other study designs for evaluating population-based interventions such as stepped-wedge approaches, through which larger clusters can be more easily created, were considered, however at the time, the statistical rigor and the practicality of these designs were in question [60, 61].

The frequency and timing of test and treat rounds in this study are based on robust mathematical models. These models account for multiple variables including LLIN coverage, usage, and baseline transmission levels. All models are based on assumptions from years of research in malaria in general, and specifically to the study site. The models suggest that clearing the parasite reservoir during the dry season, when the number of sub-clinical infections and vectors are lowest, would be the most effective way of reducing transmission, and that spacing the rounds 1–2 months from each other and ensuring at least one of the rounds is delivered immediately before the peak transmission season would be the most cost-effective way of performing this. However, model assumptions are constantly being updated as new field data are collected. Data from this study will be incorporated into the models to refine them.

## Conclusions

Ultimately, the success of MTaT campaigns in rapidly reducing malaria transmission or eliminating malaria will reside on community acceptability, the degree and duration of impact, number of years of intervention needed, and the cost-effectiveness. Data from the implementation of this study will be used to inform policy and to refine mathematical models for more precise estimates in high transmission settings.

## Abbreviations

LLIN: Long-lasting insecticide-treated net
IRS: Indoor residual spraying
ACT: Artemisinin-based combination therapy
RDT: Rapid diagnostic test
MTaT: Mass testing and treatment
MDA: Mass drug administration
KEMRI: Kenya Medical Research Institute
CDC: Centers for Disease Control and Prevention
HDSS: Health and demographic surveillance system
CHV: Community health volunteer
XSS: Cross-sectional study
PDA: Personal digital assistant
CO: Clinical officer
rRT-PCR: Real-time reverse transcriptase polymerase chain reaction
PSC: Pyrethroid spray catch
PR: Prevalence ratio
